**Primary outcomes**
Controlled blood pressure (<140/90)Controlled hemoglobin A_1c_ (in diabetes mellitus: <9%)
**Secondary outcomes**
BMI ≥25 (adults; not a formal clinical quality measure: a health outcome associated with clinical quality measure)Controlled lipids (not a formal clinical quality measure: a health outcome associated with clinical quality measure)BMI screening and follow-up (adults)Lipid therapy (coronary artery disease)Use of aspirin or antithrombotic (ischemic vascular disease)
**Potential covariates**
Patient covariates: Age, gender, race and ethnicity, primary language, poverty level, insurance status at a visit, and number of visits to that site or provider in last year (care use)Patient comorbidities: Charlson comorbidity score (modified)—an indicator of serious comorbid conditions that may shorten life expectancyVisit type:In-person, telephone, and virtualOutreach, encounterProvider type:Degree (eg, medical doctor, registered nurse, or physician assistant)Prescribing privileges (yes or no)Number of patients in panel

#### Qualitative Analyses

Consistent with the constant comparative method, analyses will be iterative and inductive. Emergent understandings will be explored in subsequent data collection [51]. An immersion-crystallization process [52], which entails multiple iterations of data immersion, reflection, and code development and application, will be used to identify themes and patterns in the data [53].

#### Mixed Methods Realist Analyses

A convergent comparative *case analysis* approach will be used [54], where qualitative and quantitative data build an understanding of the change process in each *case* (clinic). Quantitative and qualitative data will be integrated, as shown in Figure 3. Data from each case will be *merged* for analysis and then compared within and across clinics to confirm, expand on, or challenge each site’s findings. Potential context-mechanism-outcome configurations [55-58] will be proposed and then refined as analysis continues to identify context-specific components that enable the use of patient-specific social risk data in adapting treatment plans. Emphasis will be placed on factors influencing the use of patient-specific social risk data in care decisions, including the use of CDS tools, any unintended negative impacts on care processes and outcomes, and patient-provider interactions. Analyses will also explore staff and patient perceptions of how patients’ social risk data affect care and the potential to induce or obviate bias when such actions occur.

## Results

This project was funded by the National Institute on Minority Health and Health Disparities of the NIH in January 2020. The formative phase started in April 2020 and will run through July 2021. The tool build process began in May 2021 and will continue through November 2022. Most of the tool development activities occurred during the first 3 months, with additional refinements occurring over subsequent months. The pilot study, which is part of the tool development period, will take place between August 2021 and July 2022. The main trial will begin in December 2022 and conclude in May 2024; qualitative interviews and a provider card study will be conducted during this time frame. Data analysis and dissemination activities will take place between December 2023 and November 2024.

The Kaiser Permanente Northwest institutional review board reviewed the study protocol and provided approval for pilot study activities in March 2021. The institutional review board will review the protocol again before the main trial. No research with human subjects will be conducted until the proper approvals have been received.

## Discussion

### Principal Findings

Although CHCs and other primary care providers are increasingly systematizing social risk documentation, their clinical teams lack guidance on how to use these data to improve patient health and reduce inequities [30,32,59-61]. Referring patients with social risks to needed social services is associated with improved health outcomes and decreased costs [10-13,21,62-80]. Although some of these impacts may occur because social service referrals reduce social risks, recent studies have shown that health improvements subsequent to social service referrals were not mediated solely by changes in social risk status [10,81]. Little is known about how to support social risk–informed care in CHCs or other primary care settings; however, research shows that when social risk data are presented without specific care recommendations, providers use these data inconsistently [22,82,83].

CDS tools in EHRs (eg, alerts, overviews, and care gap summaries) are widely available and can enhance care quality and patient satisfaction, especially when developed with user input [24,25,27-29,84-91]. These functionalities might enhance social risk–informed care; however, we know of no prior studies examining their use in this context. This trial will address this knowledge gap by developing and testing CDS tools that suggest social risk–informed care adjustments. The CDS tools that will be tested will be developed and revised with extensive provider and patient stakeholder inputs. These tools will be designed to enable transferability to any site using the Epic EHR; general principles of using social risk data CDS for social risk–informed care will be disseminated so that similar tools can be built in any EHR system.

### Limitations and Considerations

This pragmatic trial will be conducted in CHC settings as CHCs serve patients with high rates of social risks, so study findings may not be fully generalizable to other care settings. Although the recruited CHCs will have documented social risks for ≥200 patients, few will have screened all their patients for social risks, and some will not have endorsed social risks. As a result, these tools may not be relevant to all patients. For addressing this, primary analyses will be limited to patients with known social risks, and differences between these patients and those with no social risk data will be described. Only 1-2 hours of training will be provided as implementation support to the study CHCs; more hours of training might be optimal but would not reflect real-world practices. Finally, this research was conducted in the peri-COVID period; its generalizability must be interpreted in light of the pandemic’s effects on patients’ health care access and financial security, as well as the changes it spurred in the health care sector around social care delivery [92]. The extent to which pandemic-related changes will endure is not yet clear.

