## Methods

### Setting

The study will be conducted among community health centers (CHCs) that are members of OCHIN (not an acronym). OCHIN is a nonprofit health center–controlled network that hosts a single Epic EHR for >600 primary care CHCs located across the United States. As part of previous NIH-funded studies (1R18DK105463 and 1R18DK114701) and OCHIN’s ongoing CHC-centric EHR modifications, a suite of EHR tools was designed to enable documentation of social risk data and the provision of related referrals [23,30-33]. These tools were activated OCHIN-wide in June 2016; as of April 2021, >700,000 social risk screening results in >400,000 unique patients have been documented using these tools. The tools were adapted as their implementation was based on user input and to ensure alignment with the Epic EHR’s 2018 social determinants module. At present, the tools enable users to flag targeted patients for social risk screening, select from several screening tools (Protocol for Responding to and Assessing Patients’ Assets, Risks, and Experiences; the Centers for Medicaid/Medicare Services’ Accountable Health Communities screening tool; social risk questions from the Institute of Medicine [now the National Academy of Medicine]; or individual social risk domains) [34-37], enter patient-reported social risk data via several interfaces, and allow patients to self-enter data through the patient portal or at the point of care. The tools can also be used to document patients’ priorities related to social needs and interest in related referrals. In the trial described here, the CDS tools to be developed and tested will draw information on patient-reported social risks from data documented through these existing tools.

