#### Quantitative Analyses

We will describe the percentage of clinic encounters at which (1) the CDS tools appeared to users at the intervention clinics, (2) users reviewed tool suggestions, and (3) the suggested care plan adaptations were enacted.

The primary trial outcomes are changes in the two CQMs expected to be affected by social risk–informed care: blood pressure control and HbA_1c_ control. Each CQM’s denominator will be defined according to which patients are eligible for that measure at the time of a clinic visit (eg, patients with diabetes are in the HbA_1c_ measure denominator) per national CQM measurement specifications [41]. Two-level hierarchical linear models [48-50] will be used to assess the impact of CDS tools on these outcomes. As these outcomes are binary, the generalized form of the hierarchical linear model with a log link and binomial distribution will be used. Textbox 1 shows other potential covariates; this list will be finalized based on the extent to which person-level covariates were balanced between the final intervention and control arms and will be included in the first level of the model representing the person level. The second level of the model, the CHC level, will include arm as an independent variable (control vs intervention) and a random effect for the intercept (ie, intercept-as-outcomes model). Population-averaged marginal proportions and associated 95% CIs will be calculated by arm, along with the difference between those proportions (ie, the marginal effect) and the associated 95% CI that incorporates the random effects (ie, differences between CHCs) and any included covariates.

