In secondary analyses, a repeated cross-sectional design will be used to assess the differential changes in the outcomes across time. A panel design is impractical in this population of CHC patients, so using repeated measures would result in a selective (eg, patients with stable and continuous care) and smaller sample. As we will be able to collect up to 18 months of data, we will subset the relevant patient subpopulations within clinics in 6-month increments and model time as a between-subjects effect in the model described above to evaluate the effectiveness for each outcome. More specifically, we will add time (6, 12, and 18 months) and the product of time and arm that represents their interaction in level 2 of the model. We will then calculate the population-averaged marginal proportions and associated 95% CIs by arm and time points, along with the marginal effects between arms within time points and between arms across pairs of time points (ie, differences-in-differences). Significant marginal effects between arms across time would suggest a differential change between the arms across time. As all secondary CQM outcomes (Textbox 1) are also binary, we will use the same approach to evaluate between-arm differences on these outcomes as for the primary outcomes.

Intent-to-treat analyses will be used to establish effectiveness at the population level and per-protocol analyses to assess the impact of the tools when used. For the primary analysis, depending on the size of the intraclass correlation (between 0.01 to 0.05), this study has at least 80% power to detect a 9%-17% difference in blood pressure control (n=343 per CHC; assuming baseline level of 60% blood pressure control calculated from OCHIN data) and a 10%-18% difference in HbA_1c_ control (n=214 per CHC; assuming baseline level of 34% HbA_1c_ control calculated from OCHIN data) between the intervention and control groups at a two-tailed α level of .05.

Primary and secondary analysis variables.

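### The primary population is limited to patients with known social risks, with no requirement that the risk be recorded before activation, which exposes the arm comparison to identification bias

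*Protocol article*

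**What the plan says.** The restriction appears in the protocol article under Limitations and Considerations: "primary analyses will be limited to patients with known social risks". The same paragraph says of the recruited clinics that "few will have screened all their patients for social risks", and it names one check on the restriction: "differences between these patients and those with no social risk data will be described".

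Under Quantitative Analyses, each quality measure's "denominator will be defined according to which patients are eligible for that measure at the time of a clinic visit". This is the only time anchor given for the outcome denominators. For the secondary analyses, "we will subset the relevant patient subpopulations within clinics in 6-month increments", and "we will add time (6, 12, and 18 months) and the product of time and arm". No period before activation enters that model.

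Under Setting, "the CDS tools to be developed and tested will draw information on patient-reported social risks from data documented through these existing tools". Those screening tools have been active across the whole network since June 2016, so both arms have them. Under Main Trial and Intervention, the new tools and the orientation shortly before activation go to the intervention clinics.

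The threshold of 200 screenings under Randomization and Recruitment is a criterion for clinics. It does not fix when an individual patient's risk must have been recorded.

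**The concern.** Clinics are randomised, but patients enter the primary analysis through a status that clinic staff record, and nothing in the text confines that status to the time before activation. As written, a patient first screened in month 10 could be included.

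The tools have nothing to show for a patient until a risk has been recorded, and only intervention staff are oriented to them. Staff who see the tools in use may record risks more often, or in different patients, than control staff. The two analysed groups would then differ in composition for a reason other than benefit. This is identification bias in a cluster trial: the comparison is conditioned on something that can arise after randomisation and be influenced by the arm. A shift in case mix could create, hide or inflate a difference in blood pressure or HbA1c control.

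**Working it through.** **1. When must the risk be known?** Limitations and Considerations sets the restriction without a date. Quantitative Analyses dates eligibility for the quality measure to the visit, but that concerns, for example, having diabetes, and not social-risk status. The 200-screening rule applies to clinics. The date is therefore open.

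**2. Would the planned checks show differential entry?**
- The planned description compares known-risk patients with patients who have no risk data. It is not described as a comparison of arms, or of before with after activation.
- The time model has points at 6, 12 and 18 months only. A shift that begins at activation and persists would not appear as a change between those points.
- Person-level covariates are chosen by balance between the arms. The candidates in Textbox 1 include visits in the last year and a modified Charlson score, but not the date of first screening or the number or type of risks.

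**3. The plan's own detectable differences.** Inputs from Quantitative Analyses: 343 patients per clinic and 60% control (blood pressure); 214 and 34% (HbA1c); intraclass correlation (ICC) 0.01 to 0.05; 80% power; two-sided 0.05. Clinic numbers, 6 and 30, are from Randomization and Recruitment. Effective n per arm = clinics × m / (1 + (m − 1) × ICC), normal approximation, increase from baseline:

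| Clinics | Blood pressure (points) | HbA1c (points) |
|---|---|---|
| Stated | 9–17 | 10–18 |
| 6 vs 6 | 8.8–17.2 | 9.5–18.6 |
| 6 vs 30 | 6.9–13.6 | 7.3–14.2 |

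The stated figures lie close to a 6 vs 6 calculation and are conservative for 6 vs 30. The claim of at least 80% power stands, and nothing here depends on it. The stated figures serve below as the yardstick.

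**4. Possible bias.** With no true effect, spurious difference = f × d. Here f is the excess share of post-activation entrants among the intervention arm's analysed patients, and d is the gap in control rate between later and earlier entrants, taken as the same in both arms. The document gives neither, so both are assumptions.
- Low: 0.10 × 5 = 0.5 points.
- High: 0.30 × 15 = 4.5 points.
- Wider assumptions, f from 5% to 40% and d from 5 to 20 points: 0.05 × 5 = 0.25 to 0.40 × 20 = 8 points.

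**5. Effect on type I error**, 6 vs 30 clinics. Standard error = √[p(1 − p)(1/n1 + 1/n2)], with effective n1 and n2. For blood pressure at ICC 0.01 the design effect is 1 + 342 × 0.01 = 4.42, so n1 = 6 × 343 / 4.42 = 465.6, n2 = 30 × 343 / 4.42 = 2328.1, and the standard error is 2.49 points. Rejection rate = Φ(shift/SE − 1.96) + Φ(−shift/SE − 1.96).

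| Outcome, ICC | SE (points) | Shift 0.5 | Shift 4.5 |
|---|---|---|---|
| Blood pressure, 0.01 | 2.49 | 5.5% | 44% |
| Blood pressure, 0.05 | 5.03 | 5.1% | 15% |
| HbA1c, 0.01 | 2.56 | 5.4% | 42% |
| HbA1c, 0.05 | 4.94 | 5.1% | 15% |

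The low end is harmless. The high end is not.

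**The case against.** The strongest reply is that this is a missing detail. The restriction is one sentence in the limitations of a condensed article, and the full protocol or analysis plan may set a look-back date. The surrounding text describes what recruited clinics will already have recorded, so a status-at-recruitment reading is possible. This stands in part: an unseen document may settle the matter, and the article does not say that late-recorded patients will be included. But the article does fix the primary population on a status that can change after randomisation, and that goes beyond silence.

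Four stronger readings are tempting and are not supported:
- *That the tools will raise screening, or will raise it in intervention clinics only.* The document does not say that they prompt screening. They display risks already recorded, both arms have the screening tools, and recording may rise in control clinics too. A differential change is plausible and no more.
- *That the article says social-risk status is assessed at visits throughout follow-up.* The visit anchor concerns eligibility for the quality measure.
- *That the restriction contradicts intent-to-treat.* The article contrasts intent-to-treat with per-protocol analysis of the tools when used. Analysis by assigned arm within a subpopulation is compatible with that.
- *That case mix is ignored.* Arm balance guides the choice of covariates, and visit frequency and comorbidity are candidates. Adjustment would help only as far as those variables capture the shift.

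The article also explains that following a fixed panel would favour patients in stable, continuous care. That is a real cost of freezing entry.

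**Conclusion.** The point holds as an exposure to identification bias, not as a demonstrated bias. The primary population depends on a status that can be acquired after activation, screening is incomplete, and one arm alone receives an intervention that uses that status. The planned checks would not reliably reveal or remove differential entry.

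Direction is unknown. The 0.5 to 4.5 points rest wholly on the assumed shares and gaps, and the upper figure needs both at their maximum. Set against the smallest stated detectable differences, 4.5 points is half of 9 (blood pressure) and 45% of 10 (HbA1c). If recording changes equally in both arms, or if late entrants resemble earlier ones, the bias is nil. The matter should be settled before outcome data are examined, because a cut-off chosen afterwards would look data-driven.

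**What to change.** - Define the primary cohort in both arms as patients eligible for the quality measure with a social risk recorded on or before a common activation date. Control clinics take the same calendar date. Differential entry through later recording is then zero by construction.
- Keep the open definition, including patients first recorded later, as a secondary or sensitivity analysis.
- Add a sensitivity analysis of all measure-eligible patients regardless of social-risk data.
- Report screening and risk-positive rates by arm, before and after activation.

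If the full protocol or analysis plan already sets such a date, it is enough to state it and add the reporting.

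The work is wording plus a date filter on records already held centrally. The precision cost is small. Assuming 10% to 40% fewer patients per clinic, the 6 vs 30 detectable difference for blood pressure moves from 6.9–13.6 to 7.0–13.7 (10% fewer) or 7.4–13.9 points (40% fewer). For HbA1c it moves from 7.3–14.2 to 7.4–14.3 or 8.0–14.6 points. The larger cost is to representativeness: the primary cohort omits newly screened patients to whom the tools apply and, by month 18, leans toward those with continuing care. That is why the open definition stays as a sensitivity analysis.

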### Conclusions

There are no known prior studies assessing whether and how EHR-based CDS can be used to support contextualized social risk–informed care. We believe this study will be the first to develop and test CDS tools that both highlight CHC patients’ social risks and suggest care plan adaptations based on reported social context. The tools will be developed with extensive input from CHC staff and patients to ensure patient and provider usability and acceptability. The results will yield usable data for CHCs and other primary care providers to inform strategies that can ensure new social risk screening initiatives translate to improvements in care delivery and health outcomes.

## Abbreviations

CDS: clinical decision support
CHC: community health center
COHERE: Contextualized Care in Community Health Centers’ Electronic Health Records
CQM: clinical quality measure
EHR: electronic health record
HbA_1c_: hemoglobin A_1c_
NIH: National Institutes of Health
SDH: social determinants of health
